**3.1.5 Elimination criteria**

- Participants who are subsequently found to not fulfill the inclusion criteria after the commencement of the study will be excluded.
- Subjects who decline to participate in the prescribed examination and assessment protocol during the study will be withdrawn.
- Participants demonstrating suboptimal adherence, with cumulative exercise time falling below 80% of the prescribed amount, or those who consume medication that influences muscle or bone metabolism during the study period, will be considered non-compliant and thus removed from the trial.

1. **Sample size**

The prevalence of functional falls and fractures is a significant clinical concern and a severe consequence for patients with sarcopenia, stemming from the progressive loss of muscle mass and function. The Simple Physical Performance Measurement Scale (SPPB) serves as a pivotal efficacy indicator in this context. Drawing from extant literature ^[14]^, a 24-week exercise intervention in elderly patients with a heightened risk of falls yielded an SPPB score of 9.83 ± 1.85 in the experimental group, compared to 8.39 ± 2.52 in the control group. Employing a two-sided test with an alpha level (α) of 0.05 and a power (test efficacy) of 0.9, the calculated sample size for a single group is n = 35.6, which approximates to 36 participants. Consequently, the combined sample size for both groups amounts to 72 individuals. Factoring in a dropout rate of 20%, the total sample size required for this study is 90 cases, equating to 45 participants per group.

1. **Participant**

The proposed study aims to enroll 90 elderly patients with sarcopenia who visited the Hospital of Chengdu University of Traditional Chinese Medicine between July 2022 to August 2023. The process for inclusion involves a meticulous screening of candidates at the outpatient clinic. Potential participants are to be thoroughly informed about the study’s objectives, procedures, and potential risks. Following this educational dialogue, those who meet the study criteria and express a willingness to participate will be asked to provide informed consent and sign the corresponding consent form.

1. **Randomization and Blinding**

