The random allocation sequence was delegated to a specialized statistical analyst, who utilized the SAS 9.4 software (SAS, USA) to generate a series of random numbers ranging from 1 to 90. Subsequently, the analyst enumerated the eligible participants in sequential order of their enrollment and allocated them randomly in a balanced 1:1 ratio to either the Baduanjin exercise intervention cohort—hereinafter referred to as the ‘Baduanjin group’—or the resistance training comparator arm—hereafter denoted as the ‘control group’. The integrity of the randomization sequence was preserved by the study administrator, who remained uninvolved in participant recruitment, outcome evaluation, and statistical analysis. Upon completion of all initial assessments, participants were apprised of their group assignment via telephone.

Due to the nature of the intervention, it was impracticable to blind the study participants. Consequently, blinding was confined to the outcome assessment, data management, and statistical analysis phases. In lieu of explicit group identifiers, the designations ‘A’ and ‘B’ were employed on the case report forms to maintain anonymity. An independent statistical expert, external to the participant cohort, employed SAS software to create the blind base—a table of random numbers—which was subsequently safeguarded by the study administrator. The statistician tasked with data analysis remained uninformed about the specific intervention programs administered to each group. This blinding was only disclosed subsequent to the completion of all statistical analyses.

1. **Interventions**

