**10.1 Power calculation**

The prevalence of falls and fractures due to the diminution of muscular mass and function underscores the clinical urgency and grave repercussions associated with sarcopenia. Drawing upon empirical evidence from a preceding trial targeting older adults predisposed to falls ^[14]^, the Short Physical Performance Battery (SPPB) is employed as the primary efficacy index. Utilizing a two-sided test with a power of 90% and a significance level of 5%, the requisite sample size for a single intervention group is deduced to be approximately 36. Accounting for an anticipated dropout rate of 20%, each group necessitates 45 participants diagnosed with sarcopenia.

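### 36 per group does not give 90% power on the plan's own figures: about 50 are needed, and unadjusted power at 36 is about 78%

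*Combined protocol and SAP*

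**What the plan says.** Section 4 (Sample size) makes the SPPB the efficacy measure and takes its planning values from a cited 24-week exercise trial in older people at high risk of falling. That trial "yielded an SPPB score of 9.83 ± 1.85 in the experimental group, compared to 8.39 ± 2.52 in the control group". The error rates follow: "Employing a two-sided test with an alpha level (α) of 0.05 and a power (test efficacy) of 0.9". The result is that "the calculated sample size for a single group is n = 35.6, which approximates to 36 participants", hence 72 in total, raised to 90 (45 per group) for 20% dropout.

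Section 10.1 (Power calculation) restates the 90% power and 5% two-sided level, and says that "the requisite sample size for a single intervention group is deduced to be approximately 36", again with 45 per group after dropout. Section 6 sets equal allocation: participants are "allocated them randomly in a balanced 1:1 ratio".

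Neither section names the formula or says which SD entered it. Neither mentions a correlation with baseline or any covariate adjustment in the calculation.

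**The concern.** The two quoted SDs differ considerably: 2.52² is 6.35 and 1.85² is 3.42, so the control-arm variance is nearly twice the experimental-arm variance. A two-sample calculation has to carry both. A result of about 36 per group looks too small for a difference of 1.44 with SDs of this size, and it looks like what the smaller SD alone would give.

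What is at stake is the headline design claim for the primary outcome. If it is wrong, the risk of missing the planned difference is well above the 10% that readers are told, and a non-significant result would be judged against the wrong figure. The comparator is resistance training with the same session length, weekly frequency and duration as Baduanjin (sections 7.1 and 7.2). A small or null difference is therefore a realistic outcome, and the true miss rate matters for reading it.

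**Working it through.** **Inputs**

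- Difference in means: 9.83 − 8.39 = 1.44 points (section 4).
- SDs: 1.85 experimental, 2.52 control (section 4).
- Two-sided α = 0.05, so z = 1.960. Power 0.90, so z = 1.2816 (sections 4 and 10.1).
- Allocation 1:1 (section 6). Dropout 20% (sections 4 and 10.1).

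**Step 1. Reproducing the stated 35.6.** Put SD = 1.85 in both arms:

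- Normal approximation: n = 2 × 1.85² × (1.960 + 1.2816)² / 1.44² = 34.69.
- With the usual small-sample term z²/4 = 1.960²/4 = 0.96: 35.65.
- Exact noncentral t: 35.67.

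This agrees with 35.6 and rounds up to 36. The other single-SD choices at the same α and power do not agree. The simple average of the SDs (2.185) gives 48.4 (normal) or 49.4 (t). The control SD alone gives 64.4 or 65.3.

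**Step 2. Using both SDs.**

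- Sum of variances: 1.85² + 2.52² = 3.4225 + 6.3504 = 9.7729.
- Root-mean-square SD: √(9.7729 / 2) = 2.21. Standardised difference: 1.44 / 2.21 = 0.65.
- Normal approximation: n = (1.960 + 1.2816)² × 9.7729 / 1.44² = 10.507 × 9.7729 / 2.0736 = 49.5, so 50.
- Noncentral t: 50.5, so 51.

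**Step 3. Power at the planned size, unadjusted comparison, both SDs.**

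| Method | 36 per group | 45 per group |
|---|---|---|
| t-test (noncentral t) | 77.8% | 86.3% |
| Welch test | 77.7% | 86.3% |
| Normal approximation | 78.9% | 87.1% |
| Simulation (100,000 trials) | 77.9% | not run |

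The 36 column is what remains of 45 after the plan's own 20% loss. The 45 column assumes no loss. With 36 per group, the difference detectable with 90% power is 1.71 points by the t-test, not 1.44.

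**Step 4. Dropout.** 36 / (1 − 0.20) = 45, so the plan's inflation step is correct. Applied to the corrected figure, 51 / 0.80 = 63.75, so 64 per group or 128 in total. With the normal-approximation figure of 50 it is 62.5, so 63 per group or 126 in total.

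**Step 5. Was 80% power intended?** With both SDs, 80% power needs 37.0 (normal) or 38.0 (t) per group; the simple-average SD gives 36.1 by the normal approximation. These lie near 36, but none is 35.6, and both sections state 90%.

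**The case against.** **The cause is inferred.** The plan names no SD or formula, and 35.6 can also be reached with both SDs if a correlation is brought in. A change-score analysis with a baseline-to-follow-up correlation of 0.64 gives 49.5 × 2 × (1 − 0.64) = 35.6. A baseline-adjusted analysis with a correlation of about 0.53 gives 49.5 × (1 − 0.53²) = 35.6. This stands as a limit on how firmly the cause can be stated. It does not rescue the figure, because the plan gives no correlation. Using 1.85 for both arms is the only match that needs no undocumented parameter.

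**The planned analysis is not a t-test.** Section 10.2 specifies a GEE model on repeated measures, and Table 2 schedules physical function at 0, 12 and 24 weeks. A model that uses baseline SPPB well could have more power; a change contrast with correlation below 0.5 would have less. This is fair, and 78% must be labelled as unadjusted. But the covariates section 10.2 gives as examples are age, gender and baseline muscle mass index, not baseline SPPB, and neither sample-size section claims a gain from modelling.

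**More than 36 per group may be analysed.** Section 10.2 follows intention to treat, and GEE can use partial records. Even with all 45 per group analysed, unadjusted power is 86% to 87%. The withdrawal and elimination rules in sections 3.1.4 and 3.1.5 pull the other way.

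**The SDs may not carry over.** They come from people at high fall risk, not from a sarcopenia sample. So 78% is what the plan's inputs imply, not an established property of this trial. The 90% claim rests on the same inputs.

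**Nothing else is damaged.** The error does not bias the estimate or inflate the type I error. That is true, and the point is confined to the stated power.

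**Conclusion.** The concern holds. The 36 per group in sections 4 and 10.1 does not follow from the quoted means, SDs, significance level and power. About 50 evaluable per group (49.5 normal, 50.5 t) are needed. At the plan's 36, the chance of missing a true 1.44-point difference is about 22%, not 10%; with all 45 analysed it is about 14%.

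These figures assume the quoted means and SDs, equal groups, and an unadjusted two-sided comparison at one time point. That 1.85 was applied to both arms is a strong inference, and the conclusion does not depend on it. The power stated for the primary outcome is wrong as written and must be corrected.

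**What to change.** Correct sections 4 and 10.1 together:

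- State that the calculation uses both SDs (1.85 and 2.52), and name the formula.
- Replace the 90% claim: 45 randomised per group, 36 evaluable after 20% dropout, gives about 78% power for a 1.44-point difference in an unadjusted two-sided 5% comparison. The figure with no dropout, about 86%, may be added.
- Keep the total of 90.

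If the sponsor decides to adjust the primary model for baseline SPPB, the adjusted power can be stated beside the unadjusted figure, with the assumed correlation r and its justification. Multiplying the variance by (1 − r²) at 36 per group gives about 82% at r = 0.3, 88% at r = 0.5 and 90% at r = 0.55. The documents give no value for r, so these are assumptions.

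The cost is two sentences of wording and a less favourable stated power. No extra patients are required. Keeping the 90% claim on an unadjusted basis would instead need 64 randomised per group (128 in total).

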**9.1 Quality control for researchers**

The recruitment process for the study was meticulously orchestrated to ensure the selection of appropriate subjects. Specialized recruiters conducted screenings with stringent adherence to the predetermined inclusion and exclusion criteria. Subjects who satisfied all inclusion criteria and none of the exclusion criteria were systematically enrolled and assigned a unique study number reflecting their sequential order of inclusion. Conversely, individuals who failed to meet the necessary criteria were excluded from the study. The recruiters maintained detailed records of each exclusion, documenting both the quantity and the specific reasons for disqualification.

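### A group letter on the case report forms lets one participant's remark decode every lettered form that the same assessor completes afterwards, if assessors see the letter

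*Combined protocol and SAP*

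**What the plan says.** Section 6 (Randomization and Blinding) accepts that "it was impracticable to blind the study participants". It states that "blinding was confined to the outcome assessment, data management, and statistical analysis phases". For the forms it gives one device: "In lieu of explicit group identifiers, the designations" A and B "were employed on the case report forms to maintain anonymity". The key is a random number table, "which was subsequently safeguarded by the study administrator". That person takes no part in recruitment, outcome evaluation or analysis. The analyst is not told which programme each group received until the analyses are finished.

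There are two arms, and the analyst "allocated them randomly in a balanced 1:1 ratio". After the baseline measurements, "participants were apprised of their group assignment via telephone". Table 2 then schedules physical function, grip strength, the 6 m walk and cognition at weeks 12 and 24.

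Section 9.1 gives a participant-level identifier that does not refer to the group: each enrolled person is "assigned a unique study number reflecting their sequential order of inclusion". Section 9.2 repeats this.

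**The concern.** A letter that stands in for the group name means the same thing for everyone in that group. It hides the arm only while nobody who sees the letters learns the arm of even one participant. Here every participant knows their arm, and by week 12 each has been offered three sessions a week of an exercise programme that is easy to name. An assessor who hears a single mention of it, and who has the lettered form in hand, no longer needs to be told about anyone else.

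Assessor blinding matters for this primary outcome. The SPPB (section 8.2 and Table 1) is built from timed tasks and observed balance holds, converted to points at narrow cut-points such as 4.82 s for the walk and 11.20 s for the chair stands. A small timing difference near a cut-point changes a participant's score by a whole point. If such differences ran in one direction by arm, they would feed into a comparison planned on a mean difference of 9.83 − 8.39 = 1.44 points. The documents describe no letter-free assessment form, no request to participants not to name their programme, and no record of assessor unblinding. Researchers oversee the training sessions (section 9.3), and the plan does not say whether they are separate from the assessors.

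**Working it through.** **Inputs.** Two arms, 1:1, and two letters (section 6). Sample size of 36 per group before dropout, 20% dropout, 90 in total (section 4). Follow-up assessments at weeks 12 and 24 (Table 2). The plan does not give the number of assessors, the pages that carry the letter, or the rate at which participants reveal their arm.

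**Step 1: the plan's own total.** 2 × 36 = 72, and 72 / (1 − 0.20) = 90. The figure reproduces. About 72 participants are expected to remain.

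**Step 2: what one remark reveals.** Two letters can be matched to two arms in only two ways. Knowing one participant's letter and arm rules out one of them, so a single remark fixes the meaning of both letters. With study numbers only, it fixes one participant's arm.

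**Step 3: which scores are exposed.**
- Baseline: not exposed, because participants are told their arm after these measurements.
- Follow-up scores recorded before the remark: not exposed.
- Follow-up scores recorded after it, by the same assessor, on a lettered form: exposed.
- Scores recorded by another assessor: exposed only if that assessor also learns the code, on which the plan is silent.

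**Step 4: reach under stated assumptions.** Suppose one assessor does every follow-up visit, all forms are lettered, and 72 participants attend both visits. That makes 72 × 2 = 144 visits. If the remark comes at visit j, the later visits that can be decoded number 144 − j:
- j = 1: 143
- j = 72: 72
- j = 144: 0

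With study numbers only, the count of later visits exposed is at most 1 (the speaker's own week 24 visit). With several assessors, the total in the formula is the number of visits done by the one who heard the remark.

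**Step 5: how likely one remark is.** The rate is an assumption. If each of n participants independently reveals the arm with probability p, the chance of at least one remark is 1 − (1 − p)^n:
- p = 1%: 52% for n = 72, 60% for n = 90
- p = 2%: 77% and 84%
- p = 5%: 98% and 99%
- p = 10%: above 99.9% for both

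These count a remark at any time to any assessor, so they overstate the chance of an early remark to an assessor who goes on to complete many lettered forms.

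**Step 6: bias.** Nothing in the documents says how far a knowing assessor would shift scores, so no bias in SPPB points is computed.

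**The case against.** The strongest objection is that the plan never says the assessors see the letter. It could be added at data entry or sit on a page that they do not handle. This stands as a limit, and the point is conditional on it. It does not remove the point: the case report form is where outcome data are normally recorded, the letter is the only form-level device named, and it is offered as the means of blinding for phases that include outcome assessment. If assessors work on letter-free forms, the plan should say so.

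A reader might infer that one remark unblinds all assessors to all 90 participants. The documents do not support that. Baseline and earlier scores are untouched, 20% dropout is expected, and spread from one assessor to others is not documented. Section 7.2 mentions sub-centres, so there may be several assessors.

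A reader might also infer that blinding is the only protection against detection bias. That is too strong. Table 1 uses fixed time limits, grip is read from an electronic meter as the highest of four readings, and section 9.4 refers to standardised methods. These narrow the assessor's discretion but do not replace blinding.

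Two further objections hold. Removing the letter does not stop a participant from telling the assessor their own arm. And data managers seeing which participants share a letter is ordinary A/B coding, which does not by itself reveal the programme.

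**Conclusion.** The point holds as a conditional design risk. If the assessment forms carry the letter, a remark that would reveal one participant's arm instead reveals the arm of everyone whose lettered form that assessor completes afterwards. The reach runs from no later visits, if the remark comes at the last visit, to nearly all follow-up visits, if it comes at the first and one assessor does them all.

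The conclusion rests on three readings: the letter is constant within a group, which follows from its replacing the group name; it is visible to the assessor, which is natural but unstated; and it is not on the form before a participant's baseline is scored. The documents do not show that any unblinding happened, and they do not allow the size or direction of a bias to be derived. The change is still worth making, because the letter does nothing on an assessment form that the study number does not already do.

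**What to change.** - Identify participants on all assessment forms by the existing study number only.
- Have the study administrator, who already holds the key, release the coded A/B variable to the blinded statistician after database lock. The analysis stays blinded as planned.
- Add an item to the week 12 and week 24 forms on which the assessor records whether the participant's arm became known, and how.
- Section 6 is written in the past tense, so lettered forms may already be in use. If so, document who saw them and at which visits, and report this as a limitation of the assessor blinding.

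The cost is a form change and one file transfer. The change confines a disclosure to the participant who makes it, but does not prevent that disclosure.

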**7.1 The Baduanjin Group**

In conjunction with health education initiatives, the Baduanjin training is conducted at a designated time and location. Each session is facilitated by an instructor with a minimum of five years’ experience in teaching Baduanjin. The training adheres to the Baduanjin standards promulgated by the State General Administration of Sports in 2006 ^[15]^. The sequence comprises a preparatory stance followed by a series of ten movements:

- Preparatory Posture
- Holding Up The Sky With Both Hands To Regulate The Sanjiao
- Draw The Bow On Both Sides As If To Shoot A Vulture
- Stretch Arms Asymmetrically To Enhance Spleen And Stomach Function
- Look Back To Treat Five Strains And Seven Impairments
- Sway The Head And Buttocks To Subdue The Heat Fire
- Touch Feet To Strngthen Kidneys And Waist
- Rise Up On Toes And Land On Heels Repeatedly To Cure Disease
- Clench The Fist And Open Eyes Wide To Enhance Vitality
- Closing Posture

The regimen is scheduled three times weekly, with each session lasting 60 minutes. This includes 15 minutes for warm-up activities, 30 minutes dedicated to the Ba Duan Jin exercises, and 15 minutes for cool-down activities, spanning a total duration of 24 weeks.

**7.2 The Resistance training Group**

The educational component of the study on sarcopenia in the elderly is structured to provide sessions once every four weeks, each lasting no less than 30 minutes. These sessions are designed to impart knowledge on the risk factors, adverse consequences, and preventive measures associated with sarcopenia. An example of such preventive measures includes adherence to the dietary guidelines for the elderly, as revised in 2016 by the Chinese Nutrition Society, which emphasizes rational nutrition, balanced diets, and the cultivation of healthy living and eating habits. In terms of physical intervention, the study incorporates a resistance training program tailored to the geographic location of each sub-centre. The regimen consists of 60-minute sessions conducted three times a week over a 24-week period. Each training session is segmented into a 15-minute warm-up, followed by 30 minutes of resistance exercises—including Wall squat, Wall push-up, Forward lunge, Reverse triceps push-up, and Wall-supported calf raise—and concludes with 15 minutes of cool-down activities.

**7.3 Assessment of the day-to-day activities of the intervention**

To mitigate the potential confounding impact of routine physical activities on the efficacy of the exercise intervention, participants are required to meticulously document their daily activities at the conclusion of weeks 1, 12 and 24 post-intervention commencement. This documentation encompasses the average daily activity and its corresponding duration over the preceding week. The catalog of activities spans a spectrum from sleep and sedentary work to activities of low, medium, and high intensity. The collected data, encapsulated in activity fact sheets, are subsequently retrieved via telephone follow-ups conducted by the research team.

